## Abstract

**Background:**

Influenza infections often remain undiagnosed in patients admitted to hospital due to lack of routine testing. When tested for, the diagnosis and treatment of influenza are often delayed due to the slow turnaround times of centralised laboratory PCR testing. Newer molecular systems, have comparable accuracy to laboratory PCR testing, and can generate a result in under 1 hour, making them potentially deployable as point-of-care tests (POCTs). High-quality evidence for the impact of routine POCT for influenza on clinical outcomes is, however, currently lacking. This large pragmatic multicentre randomised controlled trial aims to address this evidence gap.

**Methods and analysis:**

The FluPOC trial is a pragmatic, multicentre, randomised controlled trial evaluating adults admitted to a large teaching hospital and a district general hospital with an acute respiratory illness, during influenza season and defined by Public Health England. Up to 840 patients will be recruited over up to three influenza seasons, and randomised (1:1) to receive either POCT using the FilmArray respiratory panel, or routine clinical care. Clinical and infection control teams will be informed of the results in real time and where influenza is detected clinical teams will be encouraged to offer neuraminidase inhibitor (NAI) treatment in accordance with national guidelines. Those allocated to standard clinical care will have a swab taken for later analysis to allow assessment of missed diagnoses. The outcomes assessment will be by retrospective case note analysis. The outcome measures include the proportion of influenza-positive patients detected and appropriately treated with NAIs, isolation facility use, antibiotic use, length of hospital stay, complications and mortality.

**Ethics and dissemination:**

Prior to commencing the study, approval was obtained from the South Central Hampshire A Ethics Committee (reference 17/SC/0368, granted 7 September 2017). Results generated from this protocol will be published in peer-reviewed scientific journals and presented at national and international conferences.

**Trial registration number:**

ISRCTN17197293

Strengths and limitations of this studyThis is a multicentre randomised controlled trial.The pragmatic trial design more accurately reflects routine clinical care in a hospital setting.This is a highly relevant clinical question currently given the variable use of influenza testing and neuraminidase inhibitors in clinical practice, the ongoing threat of further influenza pandemics, the recent development of novel influenza antivirals and the undefined role of influenza point-of-care testing in acute respiratory illness during seasonal influenza.The inclusion, of some patients lacking capacity and older patients often with multiple comorbidities, makes the trial population generalisable to a secondary care population.There is ongoing uncertainty however as to how the suggested ‘test-and-treat’ strategy could be best implemented in clinical practice.

## Background

### Respiratory virus burden of disease

Respiratory tract infections are the second most common cause of mortality and morbidity worldwide,^1^ with viruses the most frequently detected pathogens in adults hospitalised with acute respiratory illness.^2^ Seasonal influenza epidemics lead to excess hospitalisations and death due to complications including pneumonia and exacerbation of underlying cardiopulmonary conditions, and occur mainly in the elderly and patients with comorbidity.^3–5^

### Influenza: widespread but underdiagnosed

Estimates of the burden of influenza virus infection in hospitalised adults have traditionally been based on the incidence of the influenza-like-illness syndrome (ILI, defined as fever of >38°C and new respiratory symptoms) which has poor sensitivity (around 50%) and specificity (0%–63%), rather than on laboratory-confirmed influenza.^6–9^ Patients may also present as decompensated cardiovascular disease, collapse or diabetic emergencies.^10 11^ A recent Canadian study estimated that only around 1 in 14 emergency department (ED) visits due to influenza virus infection was correctly attributed to influenza.^12^

Sampling for respiratory viruses is generally performed on upper respiratory tract samples; however, several recent studies suggest that in lower respiratory tract syndromes (such as pneumonia and exacerbation of chronic obstructive pulmonary disease (COPD)) testing of upper respiratory tract samples for viruses is insensitive compared with testing lower respiratory tract samples.^13 14^

For these reasons, it is likely that the burden of influenza and other respiratory viruses among hospitalised adults and its economic impact have been vastly underestimated.

### Neuraminidase inhibitors

Neuraminidase inhibitors (NAIs) such as oseltamivir (Tamiflu) are recommended by Public Health England (PHE) and WHO guidelines for all hospitalised adults with suspected and proven influenza infection.^15^ Although there have been no randomised controlled trial evaluating the efficacy of NAIs in this group, well-controlled observational data suggest that the treatment of influenza with NAIs reduces mortality in hospitalised adults, especially when commenced rapidly.^16 17^ Therefore, it is important that hospitalised patients with influenza are all identified and treated as soon as possible after presentation.

### Previous point-of-care tests (POCTs) for influenza

Rapid diagnostic tests for influenza, based on antigen detection in upper respiratory tract samples, have been available for many years but have poor diagnostic accuracy in adults, where sensitivity is around 50%.^18 19^ The poor sensitivity of these antigen-based tests has limited their clinical utility and their use was not associated with clinical or health economic benefits in a large randomised controlled trial in hospitalised adults.^20^ The current gold standard diagnostic test for respiratory viruses is laboratory-performed PCR which is highly sensitive and specific but has a typical turnaround time for results of 24–48 hours.^21^ New rapid, molecular tests have recently been developed, including the BioFire FilmArray respiratory panel. These molecular platforms are broadly equivalent in accuracy to laboratory PCR, without the need for specialist laboratory support and expertise, can provide a result in under 1 hour and can potentially be used as a POCT.

### FilmArray respiratory panel

The FilmArray respiratory panel 2 (BioFire Diagnostics, Utah, USA) uses nested real-time PCR to detect around 20 respiratory viruses. The FilmArray requires only 2 min of ‘hands on’ time and produces a test result in around 45 min.^22^ The FilmArray respiratory panel 2 is both Food and Drug Administration (FDA) cleared and CE in-vitro diagnostic (IVD) marked. The viral pathogens detected by the FilmArray respiratory panel 2 include: influenza A (H1 and H3), influenza B, adenovirus, coronaviruses (HKU1, NL63, 229E, OC43) human metapneumovirus, human rhinovirus/enterovirus, parainfluenza (types 1–4) and respiratory syncytial virus.^20 21^ The FilmArray respiratory panel is broadly equivalent in accuracy to laboratory PCR, and has been validated on nose and throat swabs, nasopharyngeal aspirates, lower respiratory tract samples and on samples from immunocompromised patients.^23–30^ These studies also show high reliability, ease of use and short turnaround times.

### Clinical impact of POCT for respiratory viruses

Though viruses are the most commonly detectable pathogen in adults hospitalised with acute respiratory illness, antibiotic use is near universal.^2^ Antibiotic overuse for acute respiratory illness is partly driven by clinical uncertainty regarding the underlying aetiology; therefore, early identification of viruses may prevent or shorten unnecessary antibiotic use. Previous small studies have suggested that rapid molecular viral testing might reduce antibiotic use and improve influenza antiviral use.^31 32^ We have recently shown in a large pragmatic randomised controlled trial (ResPOC)^33^ that routine syndromic molecular POCT for respiratory viruses (using the FilmArray respiratory panel) in adults presenting to hospital with acute respiratory illness was associated with a number of clinical benefits compared with routine clinical care including a reduction in unnecessary antibiotics use, and a reduced length of hospital stay. It also suggested improved influenza detection and antiviral use and better side room utilisation, although the number of patients infected with influenza was small and the study was not powered to evaluate outcomes in this subgroup.^33^ This follow-on study seeks to definitively evaluate the impact of routine molecular POCT for influenza on the detection of patients infected with influenza, their clinical care and outcome. Accepting the unpredictability of influenza activity year on year, this study is designed to recruit larger numbers of patients infected with influenza, and powered to evaluate the impact of POCT on national guideline recommended antiviral use. In addition, the novel use of sampling and deferred viral testing in the control group allows a direct assessment of missed diagnosis of influenza in hospitalised adults.

### Alignment with global research priorities

In addition to being focused on patient and healthcare organisation outcomes, this clinical research is strongly aligned with several global research priority initiatives including WHO’s Battle against Respiratory Viruses (BRaVe) initiative^34^ and the UK national report into antibiotic resistance.^35^ The BRaVe initiative aims to catalyse multidisciplinary research on strategies to prevent and treat medically important respiratory virus infections with the goal of timely integration of research advances into public health practice. Priority areas identified include improving diagnostic tests for viral respiratory illness and improving the clinical management of patients with acute respiratory viral illness, both addressed by this study. With the growing threat of antimicrobial resistance to global public heath, there is increasing need for the research and development of interventions which can help avoid unnecessary antibiotics use.^36^ The data that will be generated by this trial regarding the impact of influenza POCT on antibiotic prescribing is highly aligned with this global initiative.

### Added value

In addition to evaluating the clinical benefit of routine molecular POCT for influenza, we will also use this opportunity to answer other important research questions including the ideal specimens for respiratory virus testing (upper vs lower respiratory tract specimens) in patients with lower respiratory tract infection (LRTI), the difference in viral load between these two specimen type and whether changes in viral load over time (kinetics) in respiratory samples or the presence of viral RNA in the blood is related to and predictive of clinical outcome.

## Study aims and objectives

### Aims

This study aims to prospectively evaluate the impact of a routine molecular point-of-care (POC) ‘test-and-treat’ strategy for influenza in adults hospitalised with acute respiratory illness during influenza season.

### Objectives

To evaluate the impact of routine molecular POCT on the clinical management of influenza including: the detection rate of influenza, the adherence to national (PHE) influenza guidelines, the speed and appropriateness of NAI use and the speed and appropriateness of isolation facility use.To evaluate the impact of routine molecular POCT on measures of clinical effectiveness in adults hospitalised with influenza including: time to clinical stability, time on supplementary oxygen, duration of hospitalisation, adverse events and mortality.To explore the differences in viral detection between upper and lower respiratory tract samples and the changes in viral load that occur over time in NAI-treated and NAI-untreated patients.

Study processes that patient–participant will undergo are summarised in figure 1.

**Figure 1 F1:**
[figure not shown]
Participant flow through the study. NAI, neuraminidase inhibitor; NIHR WTCRF, National Institute for Health Research Wellcome
Trust Clinical Research Facility; POCT, point-of-care test.

## Methods

### Trial design

This is a pragmatic, multicentre, parallel group, open-label, randomised controlled study. Groups are allocated 1:1 to the intervention arm (POCT) and control arm (routine clinical care). This protocol adheres to the Standard Protocol Items: Recommendations for Interventional Trials statement.^37^ The study will take place across up to three influenza seasons (as defined by national PHE surveillance programmes).

### Participants, interventions and outcomes

#### Study setting

This is a multicentre study based within secondary care at University Hospital Southampton (UHS) National Health Service (NHS) Foundation Trust, Southampton, UK, and Royal Hampshire County Hospital, Hampshire Hospitals NHS Foundation Trust, Winchester, UK. Patients will be recruited from the acute medical unit (AMU) and the ED at these hospital sites.

#### Eligibility criteria

##### Inclusion criteria

Is a patient in an ED* or AMU, within UHS NHS Foundation Trust or Hampshire Hospitals NHS Foundation Trust.Aged ≥18 years old.Has acute respiratory illness**.Duration of respiratory illness less than 10 days prior to hospitalisation.Can be recruited to the study within 16 hours of presentation.

*For patients in ED, a decision will have already been made that the patient will be admitted.

**An episode of acute respiratory illness is defined as an acute pulmonary illness (including pneumonia, bronchitis and influenza-like illness) or an acute exacerbation of a chronic respiratory illness (including exacerbation of COPD, asthma or bronchiectasis). For the study, acute respiratory illness as a provisional, working, differential or confirmed diagnosis must be made by a treating clinician.

##### Exclusion criteria

Not fulfilling all the inclusion criteria.A purely palliative approach being taken by the treating clinicians.Previously included in this study and re-presenting within the last 30 days after hospital discharge.Declines nasal/pharyngeal swabbing.Consent declined or consultee consent declined.

Concurrent, prior or subsequent enrolment in an observational study is not necessarily an exclusion criterion; this is at the discretion of the chief investigator and will be assessed on a case-by-case basis.

#### Interventions

##### For both control and intervention groups

A respiratory sample will be collected by a member of research staff. A combined nose and throat swab will be taken and placed into viral transport medium. If feasible, a lower respiratory tract sample (sputum) will also be obtained.

Clinical and demographic data will be collected at the time of enrolment. Outcome data will be collected from case notes and electric health records retrospectively.

A blood sample (maximum of 21 mL) will be obtained from all willing participants, processed in the National Institute for Health Research (NIHR) Wellcome Trust Clinical Research Facility lab and stored at −80°C pending further analysis. All respiratory samples leftover from FilmArray testing may be frozen and stored for further study. Participant consent for this is included in the consent form. Patients may be approached for additional samples to be collected and stored for further study (see next for schedule of additional samples).

A letter detailing that the patient has been included in this trial will be sent to the patient’s general practitioner for information only.

##### For those randomised to the interventional arm

The nose and throat swab in viral transport medium will be analysed promptly on the FilmArray respiratory panel 2 as per training delivered by the apparatus manufacturer, used as a POCT. FilmArray machines will be located in the clinical areas for this purpose. Test results are generated in around 45 min. Where lower respiratory tract samples are also obtained, these will also be tested on the FilmArray in parallel with the nose and throat swab or sequentially.

The results of the test will be documented in the patient’s case notes and a member of the clinical team responsible for the patient will be directly informed. The participant or consultee will also be informed of the result where appropriate. The infection prevention and control team will be informed of the result within 4 hours of testing. In the event of influenza A or B being detected, clinical teams will be encouraged to offer treatment with NAIs as per national guidelines. It is known that the sensitivity of virus detection may be greater with lower respiratory tract samples versus upper tract samples in certain patients. Therefore, in patient where lower respiratory tract samples are obtained in addition to the upper respiratory tract samples, if either of the swabs are positive they will treated as infected and be reported to the clinical team and infection control team as above.

##### For those randomised to the control group

These patients will be managed according to standard clinical care as directed by their treating clinicians. Laboratory respiratory virus testing will be at the discretion of the responsible clinical team and where performed will be using laboratory PCR (in the onsite laboratory). The respiratory samples collected at enrolment will be stored at −80°C and subsequently tested by the FilmArray respiratory panel at least 30 days after collection. This will allow direct comparison of pathogens between the groups (ie, an estimate of missed diagnoses in the routine clinical care group) but will not influence participant care.

#### Additional procedures

For participants randomised to receive the intervention, who subsequently have a pathogen detected on the FilmArray respiratory panel and for all participants randomised to routine clinical care, additional respiratory samples ±an additional blood test (maximum 10 mL) may be specifically requested from the participants to study temporal changes in viral load, according to the schedule described next.

##### Schedule

The nose and throat swab and lower respiratory tract samples listed here are in addition to samples taken at enrolment (day 1) and are collected at five further time points: days 2–3, days 4–5, days 6–7, days 8–10 and days 11–14+. An additional blood sample (maximum of 10 mL) may be taken at days 5–7. The participant may decline all or any of these additional tests.

### Primary outcome

The primary outcome measure is the difference in the proportion of influenza-positive patients treated appropriately with NAI during their hospital stay (within 5 days of admission).

### Exploratory outcomes

Difference in influenza detection between upper and lower respiratory tract samples.

Difference in influenza viral load between upper and lower respiratory tract samples.

Proportion with influenza RNA detected in blood.

Changes in influenza viral load over time (kinetics) in respiratory tract samples and blood.

Response rate on the ordinal hospital recovery scale at day 4 and/or 7.

### Participant timeline

Participants are identified in the AMU and ED according to eligibility criteria by research staff. Following gaining written consent, participants are immediately randomised to the intervention group or the control group. For those patients randomised to the intervention group, a nose/throat swab is collected by a study doctor or research nurse and this is tested on the FilmArray machine. If the patient is able to produce a sputum sample, this sample will also be tested on the FilmArray machine. Results are generated in approximately 45 min and are immediately communicated to the clinical team. Clinical data are collected prospectively and retrospectively for both groups. Further nose/throat swabs, sputum samples and blood tests may be collected from patients who remain inpatients on serial follow-up visits up to day 14.

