### Primary outcome

The primary outcome (proportion of patients infected with influenza treated with NAIs) will be measured only in patients with confirmed influenza, that is, the intention-to-treat-infected (ITTI) population. Difference in proportions and unadjusted ORs will be used to compare the groups. The effect of group on the primary outcome will be further assessed using multiple logistic regression to control for the following covariates: age, sex, influenza vaccine status, receipt of antibiotics prior to admission, duration of illness, comorbidity, temperature, C reactive protein, severity of illness and clinical group.

Certain secondary outcome measures will be measured both in the entire cohort (ITT population) and in the influenza-infected cohort (the ITTI population) while others will only be measured in the ITTI population, as detailed in the outcome section. The intervention and control groups will be compared as per the primary outcome for equality of proportions for binary data and using t-tests and non-parametric equivalent tests for continuous data (eg, turnaround time) as appropriate.

In view of the clinical heterogeneity of patients infected with influenza, heterogeneity of effect among different clinical subgroups is anticipated a priori and therefore a preplanned subgroup analysis for key secondary outcome measures may be undertaken based on clinical group (exacerbation of asthma, exacerbation of COPD, pneumonia, ILI, non-pneumonic LRTI and ‘other’) and also based on receipt or otherwise of antiviral treatment (the receipt of NAIs within 5 days of admission). The interaction between clinical subgroups and allocation group will be assessed in the multiple regression models detailed above.

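### The primary (ITTI) denominator rests on enrolment specimens that, on the stated sequence, unblinded staff take after allocation, so influenza may be ascertained differently in the two arms

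*Protocol article*

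**What the plan says.** **Who is analysed.** Under Statistical methods, Primary outcome, the outcome "will be measured only in patients with confirmed influenza, that is, the intention-to-treat-infected (ITTI) population".

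**Order of steps.** The Participant timeline states: "Following gaining written consent, participants are immediately randomised to the intervention group or the control group". It goes on: "For those patients randomised to the intervention group, a nose/throat swab is collected by a study doctor or research nurse". The section on sequence generation, allocation concealment and implementation gives the same order (consent, identification number, randomisation) and mentions no sampling before allocation. For controls, the article says only that the samples are collected at enrolment.

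**Who samples.** The section for both groups assigns collection to research staff. The Blinding section says research staff are not blinded; only the data analysts are.

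**Which specimens.** Every participant has a combined nose and throat swab. On sputum, the text for both groups says "If feasible, a lower respiratory tract sample (sputum) will also be obtained". Under the interventional arm, where both specimens exist, "if either of the swabs are positive they will treated as infected". No matching sentence appears for controls.

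**Which test.** POCT-arm specimens go on the FilmArray promptly. Control specimens are frozen and "subsequently tested by the FilmArray respiratory panel at least 30 days after collection". Controls may also have laboratory PCR if their clinicians order it.

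**The concern.** Restricting the primary comparison to infected patients keeps the protection of randomisation only if infection is ascertained the same way in both arms. Here allocation is known before the specimens are taken, at least in the POCT arm, and one of the two specimens is discretionary.

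That discretion could matter. The background section describes upper-tract sampling as insensitive relative to lower-tract sampling in pneumonia and COPD exacerbation, and the interventional-arm section repeats that lower-tract samples may be more sensitive in some patients. If staff obtain sputum more readily when it will be tested at once, the POCT arm would pick up positives whose control counterparts go uncounted.

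The missing patients would not be a random subset. The Sample size section itself expects undiagnosed control cases to be untreated, and expects deferred testing to widen the difference by revealing them. The plan therefore accepts that control-arm ascertainment moves the primary effect. Likewise, controls counted as positive only because a clinician ordered PCR would tend to be those who were treated.

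Blinding the analysts cannot correct unequal sampling at the bedside. Nor can a later analysis plan change when a specimen was taken.

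**Working it through.** **Inputs from the Sample size section.** 420 per group; 25% positivity, so 420 × 0.25 = 105 positives per group (the plan rounds to about 100); NAI use 65% in controls and 85% with POCT; significance level 0.05, taken here as two-sided.

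**The plan's own figures.** Two-proportion test, pooled variance under the null. For 65% against 85% with n = 100:
- SE under the null = √(2 × 0.75 × 0.25 / 100) = 0.0612
- SE under the alternative = √((0.65 × 0.35 + 0.85 × 0.15) / 100) = 0.0596
- z = (0.20 − 1.96 × 0.0612) / 0.0596 = 1.34, power 91.0%

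With n = 105 the power is 92.3%. For 65% against 82% it is 78.2% (n = 100) or 80.2% (n = 105). The stated 90% and 80% are reproduced to within 2 points, so the issue is bias and not sample size.

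**Illustration 1: control positives missed.** Let a share d of true control positives be missed, of whom a share r received NAI. The observed control rate is (0.65 − d·r) / (1 − d). The POCT arm is held at 85%. Both d and r are assumptions; the documents give neither.

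| d | r | Observed control rate | Apparent difference | Loss from 20 points |
|---|---|---|---|---|
| 5% | 40% | 0.63 / 0.95 = 66.3% | 18.7 | 1.3 |
| 5% | 0% | 0.65 / 0.95 = 68.4% | 16.6 | 3.4 |
| 10% | 40% | 0.61 / 0.90 = 67.8% | 17.2 | 2.8 |
| 10% | 0% | 0.65 / 0.90 = 72.2% | 12.8 | 7.2 |

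In counts, 105 × 0.65 = 68.25 treated controls. Losing 5 untreated positives gives 68.25 / 100 = 68.2% and power of 81.4%. Losing 10 gives 68.25 / 95 = 71.8% and power of 62.3%. Both compare with 92.3% when none are lost.

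**Illustration 2: positives found only by clinician-ordered PCR are added to controls.** If all were treated, 5 extra give (68.25 + 5) / 110 = 66.6% and 10 extra give (68.25 + 10) / 115 = 68.0%. The 20-point difference falls by 1.6 and 3.0 points.

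**Direction.** If the missed positives are treated at 65%, there is no bias: (0.65 − 0.65d) / (1 − d) = 0.65. If all of 10 missed control positives had been treated, the control rate would be 58.25 / 95 = 61.3% and the apparent difference 23.7 points. The sign therefore depends on r, which is unknown.

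**The case against.** The strongest reply is that core ascertainment is planned alike. Both arms have the same swab, the same optional sputum and the same panel. The control text speaks of respiratory samples in the plural being tested later, for the stated purpose of comparing pathogens between the groups. The timeline ties sputum to whether the patient can produce it, and the trial wants control sputum for its upper-versus-lower comparison. All of this stands. It rules out saying that the arms are ascertained differently, and leaves only that they may be.

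Three further points stand:
- Sampling after allocation is explicit only for the POCT arm.
- The either-specimen sentence concerns reporting to clinicians and infection control, and the article does not say whether it also defines the analysis population. The bare definition of confirmed influenza may sit in the full protocol or analysis plan, so its absence here is no fault.
- The loss rates above are assumed. The article describes the FilmArray as broadly equivalent to laboratory PCR, so 5-10 PCR-only positives among about 105 may be generous.

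Missing untreated controls, or adding treated ones, shrinks the POCT advantage. In a superiority trial that costs power and does not manufacture a benefit.

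Two stronger readings are tempting but unsupported. First, serial samples may be requested in the POCT arm only after a pathogen is detected, but "for all participants randomised to routine clinical care, additional respiratory samples" may be requested without that condition. A reader might infer that extra control positives enter the denominator. However, the stated purpose is change in viral load, kinetics are listed as exploratory, and nothing counts these samples towards confirmation. Second, "Declines nasal/pharyngeal swabbing" is an exclusion criterion although swabbing follows randomisation. A reader might see a contradiction, but consent covers the swab and precedes allocation, so refusal can be established then.

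The reply does not remove the order of steps: unblinded staff collect a discretionary specimen after allocation, at least in the POCT arm.

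**Conclusion.** The point holds in a limited form. On the stated sequence, membership of the primary population depends on specimens collected after allocation by staff who know the arm. Sputum is optional, and the either-specimen rule is written for one arm only. Ascertainment of influenza may therefore differ between arms despite the common swab and panel.

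Under the assumed 5-10% loss of control positives with 0-40% of them treated, the effect would be about 1 to 7 points of the 20-point target, towards a smaller difference. The 7-point end is the extreme corner: 10% lost and none treated. The documents do not establish that any such loss occurs, or its size or direction. This is a cheap protection worth adopting, not evidence that the primary comparison is invalid.

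**What to change.** 1. Collect the enrolment nose/throat swab, and sputum where the patient can produce it, after consent and before the allocation code is generated, in both arms. State this order in the Participant timeline and in the section on allocation.
2. State one rule, the same in both arms, for primary ITTI membership, based on FilmArray testing of enrolment specimens only. For example, use the nose/throat swab, with a sputum-inclusive population as a sensitivity analysis. An either-enrolment-specimen rule applied to both arms would also be symmetrical, but it relies more on equal sputum collection.
3. Keep positives found only by clinician-ordered PCR out of the primary denominator.
4. Report by arm the proportion of patients who provided sputum and the number positive on sputum alone.

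**Cost.** Two bedside steps are reordered, and a sentence is added to the population definition. No procedure is added, since every participant is already swabbed. Under a swab-only rule, a few sputum-only positives leave the primary denominator. What is reported to clinical and infection control teams need not change. The new order can protect only patients enrolled after it is adopted.
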